**Discussion:**

This project is the first comprehensive research project to assess whether social support influences adherence to an activity advice outside the clinical setting without supervision of a healthcare provider. Where evidence of influence on social support is lacking, findings may have implications for the management of patients with low back pain. In addition, findings may enable physiotherapists to predict in which patients with low back pain an activity advice with social support makes sense.

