#### Secondary outcomes

2.3.3

The Social Support Scale is a study specific questionnaire and assesses the rate of social support perceived by the patient and performed by the partner (Appendix 1). This questionnaire must be filled in by the patient and the partner after the investigation period and has dichotomous outcomes.

The Dutch Illness Perceptions Questionnaire Short‐form (DIPQ‐S) assesses patients' and partner/friends' illness beliefs (Appendix 1). Eight items about illness beliefs are scored on a 0–10‐point scale, one item is an open question. The questionnaire has good reliability and validity (Broadbent et al., 2006; de Raaij, Schröder, Maissan, Pool & Wittink, 2012; Leysen et al., 2015). The DIPQ‐S will be filled in at baseline, 1, 6 and 12 weeks follow up by the patient and at baseline, 1 and 12 weeks follow up by the partner or friend.

The module attitude and intention (MAI) of The Knowledge, Attitude, Self‐efficacy and Self‐regulation, Exercise and Social Support for Sports and Exercise Questionnaire will be used to assess attitude and intention to be physically active (Wink, van Woerkom & Renes, 2006). Attitude (6 items) can be scored from 6 (most negative) to 42 points (most positive), while intention (3 items) can be scored from 3 (most negative) to 21 points (most positive). Validity of this questionnaire is unknown, but it was used in the FLASH! Campaign from the Dutch Institute for Sport and Exercise in 2003–2006 (Appendix 1). This questionnaire will be filled in at baseline and after 12 weeks by the patient and partner or friend.

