### Statistical methods

2.9

To analyse the data SPSS version 25.0 (IBM SPSS, Chicago, IL, USA) will be used. For demographic data descriptive statistics will be used and normality assumptions for the variables will be checked. An intention‐to‐treat analysis will be used for the main outcome. To correspond to the primary aim of the study, outcomes of the Activ8 will be dichotomized into adherent and not adherent patients in the intervention and control group. The Chi^2^ test will be used to investigate if there is a significant difference in the proportion of adherent patients to the activity advice between the intervention and control group after one, six and 12 weeks, and if there is a significant difference in the proportion of adherent patients between patients who experienced social support or not on the social support scale after 12 weeks. A Time Series Analysis will be used to present changes over time in perceived illness beliefs of patients and partner/friend. To understand whether illness beliefs influence adherence, Pearson's r between outcomes of the IPQ‐S at baseline and after 12 weeks and (non)adherence measured by the Active8, will be calculated, and linear regression will be used for modelling the relationship between these outcomes. To assess the correlation between attitude and intention to physical activity (MAI) and adherence at 12 weeks, Pearson's will be calculated, and linear regression will be used for modelling the relationship between these outcomes. Influence of age, gender, education level, comorbidity (CIRS), pain (VAS) and disability (QBPDS) on adherence, will be estimated by multiple regression analyses. A *p* value of <0.05 will be considered statistically significant.

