## DISCUSSION

3

This project is the first comprehensive research project to assess whether social support influences adherence to an activity advice outside the clinical setting without supervision of a healthcare provider. Unique in this study is that intervening on illness beliefs will be provided to patient and partner to minimize the influence of maladaptive illness beliefs on adherence. Literature mentions that intervention on illness beliefs changes outcomes of the DIPQS, however, responsiveness of the questionnaire is lacking (Broadbent et al., 2015). Despite this, it is of interest if a tendence of change over time may occur and influence outcomes of adherence.

Where evidence on clinical barriers is conflicting and limited, complementary, influence of age, gender, education level, comorbidity, attitude and intention to physical activity and perceived pain and disability on adherence will be investigated. Findings have implications for the management of patients with low back pain, enabling prediction as to which low back pain patient giving an activity advice with social support makes sense.

It is important to note the variation in how concepts of (non)adherence are operationalized in existing literature resulting in variable outcomes (Essery et al., 2017; van Koppen et al., 2020). For robust outcomes in this study an accurate definition of the activity advice is applied, mentioning frequency and duration, and outcomes of adherence are dichotomous, measured with a validated move monitor.

Strengths of the study are the concealed allocation and the randomization. To reduce the presence of observer bias, measurements will not be performed by the treating physiotherapist.

Treatment of both groups in one physiotherapy practice is preferred to overcome selection bias. This implicates that despite the standardized protocol and the strict requirements to ensure blinding, it is possible that patients and treating physiotherapist exchange information about the interventions. This may influence outcomes and is therefore a limitation of the study.

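### One p<0.05 rule covers at least 11 unordered secondary and predictor tests with no exploratory label, while the article says the factor results will enable prediction for practice

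*Protocol article*

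**What the plan says.** Section 2.9 (Statistical methods) describes, besides the arm comparison, these analyses against adherence:

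- a chi-square comparison of adherence "between patients who experienced social support or not on the social support scale after 12 weeks";
- Pearson correlation and linear regression between the illness-perception score "at baseline and after 12 weeks and (non)adherence measured by the Active8";
- the same two methods for attitude and intention, introduced with "To assess the correlation between attitude and intention to physical activity (MAI) and adherence at 12 weeks";
- a multivariable model: "Influence of age, gender, education level, comorbidity (CIRS), pain (VAS) and disability (QBPDS) on adherence, will be estimated by multiple regression analyses".

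The section then closes with one threshold for everything: a p "value of <0.05 will be considered statistically significant".

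The Introduction names one primary objective, the randomised comparison. It places perceived support and the patient factors under secondary objectives and states as a hypothesis that the factors influence adherence. The article does not order the secondary tests, divide alpha among them or call them exploratory.

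On the use of the results, the Discussion paragraph of the Abstract says that "findings may enable physiotherapists to predict in which patients with low back pain an activity advice with social support makes sense". Section 3 (Discussion), directly after listing the factors, is firmer: "Findings have implications for the management of patients with low back pain, enabling prediction as to which low back pain patient giving an activity advice". The rest of that sentence makes clear that the advice meant is the socially supported form.

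**The concern.** Leaving secondary tests unadjusted is ordinary when they are presented as exploratory. Here they share the threshold of the primary comparison, and the text gives their results a practical use in selecting patients. Under the plan as written, any single factor that falls below 0.05 can be announced as a significant influence on adherence and carried into a statement about whom to advise. With this many tests, an isolated p<0.05 is weak evidence.

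A second gap makes the prediction statement harder to support. Section 2.9 relates the factors to adherence overall and describes no analysis of whether a factor changes the effect of the intervention. A factor that truly predicts adherence need not identify the patients who adhere better because of social support.

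**Working it through.** **Plan's own figure.** The document gives a per-test threshold of 0.05 and no family-wise figure. For one test, 1 − 0.95 = 0.05, so there is nothing further to reproduce. Two-sided tests are assumed, as section 2.9 does not state sidedness.

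**Counting the tests (section 2.9).**

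| Analysis against adherence | Minimum count |
|---|---|
| Perceived support, yes or no | 1 |
| Illness beliefs, baseline and 12 weeks, one total score | 2 |
| Attitude; intention | 2 |
| Age, gender, education, CIRS, VAS, QBPDS | 6 |
| Total | 11 |

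Pearson's r and a one-predictor linear regression on the same pair give the same p-value, so each pair counts once. The arm comparisons at 1, 6 and 12 weeks and the time-series description of illness beliefs are left out.

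The count can rise. Section 2.3.3 says "Eight items about illness beliefs are scored on a" 0–10 scale. Tested singly at both times, the items give 8 × 2 = 16 tests instead of 2, so 1 + 16 + 2 + 6 = 25. If attitude and intention are each used at baseline and at 12 weeks, the total is 1 + 16 + 4 + 6 = 27.

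**Chance of at least one p<0.05 when all associations are null, independent tests:** 1 − 0.95^m.

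- m = 11: 1 − 0.95^11 = 0.431
- m = 25: 1 − 0.95^25 = 0.72
- m = 27: 1 − 0.95^27 = 0.750

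The expected number of false positives does not depend on correlation: 11 × 0.05 = 0.55, and 27 × 0.05 = 1.35.

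**Allowing for correlation, m = 11.** The document gives no correlations, so these are assumptions. For 11 equally correlated normal test statistics (400,000 draws):

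| Correlation between test statistics | P(at least one p<0.05) |
|---|---|
| 0 | 0.431 |
| 0.3 | 0.373 |
| 0.5 | 0.303 |
| 0.7 | 0.223 |

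**Simulating the planned tests.** Data were generated for 142 patients (the evaluable number in section 2.5), with 40% adherent (assumed) and adherence unrelated to all 11 variables. The tests were the chi-square, the four Pearson tests and the six coefficients of one multiple regression, over 6,000 runs. With correlations between the variables of 0, 0.2, 0.4 and 0.6, at least one p<0.05 occurred in 42.5%, 42.3%, 40.4% and 38.1% of runs. Moderate correlation between the predictors therefore lowers the rate only a little.

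**If some associations are real.** Only the null ones can be false positives. Under independence, 8 nulls give 1 − 0.95^8 = 0.337 and 6 nulls give 1 − 0.95^6 = 0.265.

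**Prediction statement set beside the planned analyses.** The Abstract and section 3 speak of the patients in whom advice with social support makes sense. That concerns a difference in treatment effect between kinds of patients. Section 2.9 plans only associations between factors and adherence, and names no factor-by-arm term. The gap would remain even if every association were tested with strict error control.

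**The case against.** The strongest reply is that this is normal practice. The Introduction separates one primary objective from the secondary ones, sections 2.3.2 and 2.3.3 separate the outcomes in the same way, and section 2.5 sizes the trial on the arm comparison at 12 weeks. Handling of multiplicity among secondary analyses is often left to a statistical analysis plan, which is not shown here. Much of the wording on factors is also descriptive: correlations are calculated and influences estimated, and the Abstract says only that findings may enable prediction.

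Much of this stands, and it rules out several stronger readings that a reader might infer:

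- *The plan has no hierarchy.* It has one between primary and secondary objectives. What is absent is an order within the secondary tests.
- *The plan breaks a promised 5%.* It promises none for this family. The 43% describes what the per-test rule implies and contradicts no stated figure.
- *The false-positive rate is 30–43%.* That holds for exactly 11 tests, all null, with test statistics correlated between about 0.5 and 0. More tests raise the rate; real associations or stronger correlation lower it. The Introduction itself cites evidence that some of these factors are related to adherence.
- *Sizing the trial only for the arm comparison leaves these tests unprotected.* Sample size governs power. A larger trial would not reduce the type I error of a 0.05 test.
- *A correction such as Holm is required.* For analyses labelled exploratory this is a debatable trade-off, and it would not repair the prediction statement.

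The reply does not remove the point itself. The blanket threshold is stated in the text, so it is not a matter of silence. The factors are put forward as hypotheses, and section 3 says without a hedge that the findings enable prediction.

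**Conclusion.** The point holds as a matter of labelling and interpretation. Section 2.9 lets any of at least 11 secondary or predictor tests be declared significant at 0.05, and the Abstract and section 3 give those results a predictive use that the planned analyses cannot support.

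If all 11 associations were null, at least one would reach p<0.05 in about 43% of trials under independence. The figure is about 38–43% in the simulation of the planned tests with predictor correlations of 0 to 0.6, and about 30% if the test statistics themselves correlate at 0.5. These figures rest on the global null, the minimum count and the assumed correlations.

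The randomised primary comparison is not affected. The change is worth making because it costs little and alters what may be concluded from a single factor.

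**What to change.** 1. In section 2.9, limit the significance rule to the primary arm comparison.
2. Add there that the perceived-support, illness-belief, attitude and intention, and patient-factor analyses are exploratory and will be reported as estimates with 95% confidence intervals, without claims of significance.
3. In the Discussion paragraph of the Abstract and in section 3, describe the factor findings as hypothesis-generating. Drop the statement that they enable prediction of the patients in whom advice with social support makes sense.

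Holm's procedure is optional and needed only if the sponsor wants a confirmatory secondary claim. The tests in that family would then have to be listed in advance; with 11 tests, the first step is 0.05/11 = 0.0045.

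The cost is wording only, with no new patients, data or redesign. The downside is that single factor associations can no longer be announced as significant or, if Holm is used, must meet a smaller p-value.

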### Data monitoring

2.10

Regular walking and cycling are not associated with adverse effects for NSLBP; there is no formal proof that any of these physical activities have harmful effects. The social support and treatment of illness beliefs described in this study are designed for better outcomes of physical activity levels and have no proven negative influence on pain and disability in NSLBP sufferers. Patients in both groups receive concomitant best evidence healthcare according to the Dutch guideline for low back pain (Staal et al., 2013). Therefore, composition a data monitoring committee is not needed.

### Harms

2.11

Spontaneously reported adverse events and other unintended effects of trial interventions or trial conduct are not expected. When harms occur, it will be registered by the assessor and reported to the METC Zuyderland‐Zuyd.

### Ethics

2.12

The study is subject to the Medical Research Involving Human Subjects Act (WMO) and has been approved by The Central Committee on Research Involving Human Subjects (CCMO), named METC Zuyderland‐Zuyd with Approval Number NL58005.096.16.

All amendments, protocol deviations and SUSAR's will be notified to the METC Zuyderland‐Zuyd. The investigator will notify the METC Zuyderland‐Zuyd of the end of the study within a period of 8 weeks. The end of the study is defined as the last patient's last visit. In case the study is ended prematurely, the investigator will notify the METC Zuyderland‐Zuyd within 15 days, including the reasons for the premature termination. Within 1 year after the end of the study, the investigator will submit a final study report with the results of the study, including any publications/abstracts of the study, to the METC Zuyderland‐Zuyd.

This research does not receive any specific grant from funding agencies in the public, commercial, or non‐for‐profit sectors. This paper presents independent research for which no conflicts of interest are to declare.

## DISCUSSION

3

This project is the first comprehensive research project to assess whether social support influences adherence to an activity advice outside the clinical setting without supervision of a healthcare provider. Unique in this study is that intervening on illness beliefs will be provided to patient and partner to minimize the influence of maladaptive illness beliefs on adherence. Literature mentions that intervention on illness beliefs changes outcomes of the DIPQS, however, responsiveness of the questionnaire is lacking (Broadbent et al., 2015). Despite this, it is of interest if a tendence of change over time may occur and influence outcomes of adherence.

Where evidence on clinical barriers is conflicting and limited, complementary, influence of age, gender, education level, comorbidity, attitude and intention to physical activity and perceived pain and disability on adherence will be investigated. Findings have implications for the management of patients with low back pain, enabling prediction as to which low back pain patient giving an activity advice with social support makes sense.

It is important to note the variation in how concepts of (non)adherence are operationalized in existing literature resulting in variable outcomes (Essery et al., 2017; van Koppen et al., 2020). For robust outcomes in this study an accurate definition of the activity advice is applied, mentioning frequency and duration, and outcomes of adherence are dichotomous, measured with a validated move monitor.

Strengths of the study are the concealed allocation and the randomization. To reduce the presence of observer bias, measurements will not be performed by the treating physiotherapist.

Treatment of both groups in one physiotherapy practice is preferred to overcome selection bias. This implicates that despite the standardized protocol and the strict requirements to ensure blinding, it is possible that patients and treating physiotherapist exchange information about the interventions. This may influence outcomes and is therefore a limitation of the study.

## IMPLICATIONS ON PHYSIOTHERAPY PRACTICE

4

When effectiveness of social support on adherence in NSLBP patients is demonstrated, in a patient centred approach, it can help to achieve patients' health goals.

A simple low‐cost intervention, not requiring additional education, can be added as a treatment option to increase patient relevant outcomes.

## ETHICS STATEMENT

All amendments, protocol deviations and SUSAR's will be notified to the METC Zuyderland‐Zuyd. The investigator will notify the METC Zuyderland‐Zuyd of the end of the study within a period of 8 weeks. The end of the study is defined as the last patient's last visit. In case the study is ended prematurely, the investigator will notify the METC Zuyderland‐Zuyd within 15 days, including the reasons for the premature termination. Within 1 year after the end of the study, the investigator will submit a final study report with the results of the study, including any publications/abstracts of the study, to the METC Zuyderland‐Zuyd.

## PATIENT CONSENT STATEMENT

Not applicable.

## PERMISSION TO REPRODUCE MATERIAL FROM OTHER SOURCES

Not applicable.

## STUDY REGISTRATION

The study is registered at ClinicalTrial gov NCT02996955.

## Data Availability

Data sharing is not applicable to this article as no new data were created or analyzed in this study.
